### **The Specific Aims of the project are:**

- Aim 1:** Provide training in meditation-based clinical trials for affective disturbances, psychophysiology, biostatistics research methods, and ethical conduct in research.
- Aim 2:** To create two separate treatment modules with specific criteria for the two core components and practices of attention training/focused awareness (FA) and acceptance/open monitoring (OM)
- Aim 3:** To establish the effect sizes of FA and OM vs the standard MBCT package in a controlled trial in individuals with mild-severe depression and persistent negative affect.
- Aim 4:** To assess and compare the effects of FA, OM and MBCT on subjective and objective measures of 3 domains of PFC functioning: 1) attention, 2) emotional reactivity/regulation and 3) wakefulness.
- Aim 5:** To determine which neurobehavioral processes (attention, emotion regulation, wakefulness) drive the clinical benefits of mindfulness training, independent of treatment allocation or practice type.

The findings from this K23 proposal will provide pilot data for a future R01 application for a definitive test of the practice-specific mechanisms of action and contributions to clinical benefit.

## **3. BACKGROUND AND SCIENTIFIC RATIONALE**

### **3.1 Background Information**

*NCCAM's overarching research priority is to investigate "CAM interventions used frequently by the American public, and on the conditions for which they are most frequently used" (NCCAM, 2009b)*

**Meditation is one the most popular and fastest growing CAM therapies**, attracting over a million new meditators per year in the United States alone (Barnes et al., 2008). The main reason Americans use meditation is for the alleviation of emotional distress, including mild-severe depression, anxiety and stress, and to promote wellbeing (NCCAM, 2009a). Meditation-related Medline articles have tripled in the last 3 years and NIH-funded clinical trials of meditation have increased more than 20-fold since 2000.

**Meditation's popularity is outpacing empirical support.** A 2007 government report on "Meditation Practices for Health: State of the Research" (Ospina et al., 2007) concluded that "as a whole, firm conclusions on the effects of meditation practices in healthcare cannot be drawn based on the available evidence" (pg. 210). The lack of evidence is not due to a paucity of studies (>813 studies reviewed) or a lack of randomized controlled trials (286 RCTs included).

**The central obstacle in meditation research is the nearly complete absence of delineation of the different types of meditation practices,** both in terms of their operational descriptions and separate (or additive) effects on outcomes. The report on meditation research concludes, "the field of research on meditation techniques and their therapeutic applications has been clouded by confusion over what constitutes meditation.... Further research needs to be directed toward distinguishing the effects and characteristics of the many different techniques falling under the rubric "meditation"(pg 209) and "systematically comparing the effects of different meditation practices that research shows have promise "(pg. 208). In 2008, NCCAM requested research that "develops precise criteria for specific meditation practices(NCCAM, 2008).

**Mindfulness is the fastest growing form of meditation.** More than any other form of meditation, mindfulness meditation has shown an unprecedented expansion throughout mainstream psychiatry and has been touted as the "Third Wave of Behavior Therapies"(Rapgay & Bystrisky, 2009).

**Mindfulness is comprised of two distinct components and practices that are rarely separated:** attention training and emotional non-reactivity or acceptance (Bishop et al., 2004; Rapgay & Bystrisky, 2009). Attention regulation and the ability to sustain attention is thought to be cultivated through the practice of focused awareness (FA) while a non-judgmental, accepting attitude is thought to be cultivated through the practice of open monitoring (OM)(Lutz et al., 2008; Rapgay & Bystrisky, 2009). These two components and practices are delivered in an integrated way in popular therapies like Mindfulness-Based Stress Reduction (MBSR) and Mindfulness-Based Cognitive Therapy (MBCT). However, FA and OM are thought to have different neural underpinnings and different cognitive affective and behavioral consequences (Lutz et al., 2008; Rapgay & Bystrisky, 2009). While both of these components and practices are the foundation of mindfulness-based therapies, it is unknown what contribution each component/practice makes to therapeutic outcome or by what cognitive or biological mechanism. By delineating mindfulness into its separate components, this project will address the largest confound and obstacle in meditation research. By providing knowledge about the relative benefits of different meditation practices, this project will be able to separate the active ingredient(s) from non-beneficial components and practices.

**NCCAM Priority: Clarify the neurobiological mechanisms that underlie meditation's impact on mental health and wellbeing** (NCCAM, 2008). Knowing that a specific meditation practice is effective at improving affective disturbance is not enough, we also need to know *how* and *why* it is effective.

Meditation is hypothesized to exert its therapeutic effects on affective disturbances by strengthening networks of the prefrontal cortex (PFC) (Chambers et al., 2009; Creswell et al., 2007; Davidson & Lutz, 2008; Hofmann & Asmundson, 2008; Teasdale et al., 1995; Way et al., in press) which regulates emotional reactivity, attention, and wakefulness. This hypothesis is based on the following:

a) Meditation restores PFC deficits and associated affective disturbances: Emotional disturbances characterized by high negative affect are associated with PFC hypoactivity (Clark et

al., 2009; Couyoumdjian et al., 2009), and restoration of PFC functioning parallels response to treatment in both pharmacological and behavioral interventions (Davidson et al., 2003; Hugdahl et al., 2007; Liotti & Mayberg, 2001; Liotti et al., 2002). Meditation practice, widely defined, is associated with increased activity in the PFC, (Baerentsen, 2001; Brefczynski-Lewis et al., 2007; Creswell et al., 2007; Farb et al., 2007; Herzog et al., 1990; Holzel et al., 2007; Jevning et al., 1996; Khushu et al., 2000; Lazar et al., 2000; Newberg et al., 2001; Ritskes R et al., 2003), larger frontal gray matter volumes (Holzel et al., 2008; Lazar et al., 2005; Luders et al., 2009; Pagnoni & Cekic, 2007) and decreased levels of negative affect, anxiety and depression (Allen et al., 2006; Grossman et al., 2004; Jain et al., 2007; Kabat-Zinn, Massion, Kristeller, Peterson, Fletcher, Pbert, Linderking et al., 1992; Kenny & Williams, 2007; Kuyken et al., 2008; Shapiro et al., 1998; Specia et al., 2000; Witek-Janusek et al., 2008).

**b) Meditation improves PFC-related emotional regulation:** The PFC exerts inhibitory control on limbic structures such as the amygdala (Davidson et al., 2000; Mayberg et al., 1999; Ochsner et al., 2002; Ochsner & Gross, 2005; Ochsner et al., 2004; Urry et al., 2006). Lack of such inhibitory control results in a hyperactive amygdala (Siegle et al., 2002; Siegle et al., 2007) and an associated increase in emotional reactivity, sympathetic hyperarousal and affective disturbance (Baxter et al., 1989; Bench et al., 1993; Blumberg et al., 2004; Clark et al., 2002; Davidson, 2000; Mayberg et al., 1999; Meyer et al., 2004; Siegle & Hasselmo, 2002; Siegle et al., 2002). Meditation training is associated with greater PFC inhibition of the amygdala (Brefczynski-Lewis et al., 2007; Creswell et al., 2007; Farb et al., 2007; Holzel et al., 2010; Way et al., in press), less emotional reactivity (Arch & Craske, 2006, 2010; Brewer et al., 2009; Broderick, 2005; Campbell-Sills et al., 2006; Creswell et al., 2007; Erisman & Roemer, 2010; Goldin & Gross, 2010; Kuehner et al., 2009; McKee et al., 2007; Ortner et al., 2007; Pace et al., 2009; Proulx, 2008; Raes et al., 2009; Tang et al., 2007; Vujanovic et al., 2007; Weinstein et al., 2009), and decreased sympathetic hyperarousal ([name], Bootzin, Haynes et al., 2010; Carlson et al., 2007; Maclean et al., 1994; Sudsuang et al., 1991).

**c) Meditation improves PFC-related attention capabilities:** The PFC is involved in different forms of attention including orienting, executive function and alerting (Fan et al., 2002; Fan et al., 2003). Insufficient PFC activation is associated with deficits in attention, such as "difficulty concentrating and making decisions", which are hallmark symptoms of depression. Meditation training is associated with better performance on a wide range of prefrontally-mediated attention tasks (Brefczynski-Lewis et al., 2007; Bushnell, 2009; Chambers et al., 2008; Chan & Woollacott, 2007; [name] et al., 2007; Lutz et al., 2009; Pagnoni & Cekic, 2007; Slagter et al., 2007; Srinivasan & Bajjal, 2007; Tang et al., 2007; Valentine & Sweet, 1999; Wenk-Sormaz, 2005).

**d) Meditation is associated with increased wakefulness:** High levels of blood flow and cerebral metabolic rate in the PFC correspond to alert wakefulness (Buchsbaum et al., 1989; Maquet et al., 1990; Sawaya & Ingvar, 1989), while a hypoactive PFC is associated with fatigue, tiredness and increased sleep propensity (Braun et al., 1997; Buchsbaum et al., 1989; Maquet et al., 1996). Six cross-sectional studies have found EEG-based evidence for increased wakefulness and decreased sleep propensity in meditators (Banquet & Sailhan, 1974; Cahn et al., in press; Cahn & Polich, 2009; Elson et al., 1977; Kaul et al., 2010; Mason et al., 1997) but longitudinal evidence with MBSR interventions is largely based on subjective reports (Carlson & Garland, 2005; Cohen et al., 2004; Singh et al., 1998; Surawy et al., 2005; Tang et al., 2007). In the first objective EEG-based longitudinal RCT of meditation and sleep propensity, I found increased wakefulness and decreased sleep propensity following MBCT that was correlated with improved

depression and meditation practice amount ([name], Haynes et al., 2010) (see Preliminary Studies section).

Together, these studies support the idea that strengthening PFC functioning plays a key role in meditation's beneficial effects. It is unknown which PFC process (attention, emotion regulation, wakefulness) are the most important. This study aims to investigate which of these *processes* (independent of practice type) drives clinical benefit in affective disturbances.

Current research has obscured the relationship between practice type and mechanism. All of the prior studies listed above have either used cross-sectional studies of experienced practitioners or heterogeneous treatment packages that obscure practice specific effects. It is assumed that FA training improves attention and OM improves emotional reactivity (Lutz et al., 2008), but because these practices have never been separated in research, these assumptions about practice-specific effects are untested.

To test these assumptions about practice specific mechanisms of action, this study will create separate practice criteria for focused awareness and open-monitoring/acceptance practices, compare their clinical efficacy for affective disturbance and investigate their *separate* effects on attention, wakefulness, and emotional reactivity/regulation. By knowing the specific processes that are affected by each practice, clinicians may be able to tailor treatments based on specific needs (attention deficits, emotion regulation problems etc.).

## B. INNOVATION

***B1. This study is innovative because it addresses multiple methodological limitations of prior studies.***

In addition to the central flaws of inadequate practice delineation and understanding of mechanism, mindfulness treatment research has been plagued by a number of other methodological limitations including lack of 1) active control groups 2) objective or physiological measures 3) protocol adherence and participant skill acquisition (treatment fidelity) and lack of generalizability due to condition-specific adaptations (Ludwig & Kabat-Zinn, 2008).

Therefore this study aims to address these barriers by 1) delineating mindfulness into its two core components 2) comparing these components in a controlled trial against the standard (active) treatment 3) using both subjective and objective/physiological measures, 4) carefully operationalizing and monitoring precise treatment criteria adherence and skill acquisition and 5) choosing a sample population that represents the unifying feature of all mindfulness interventions: mild-severe affective disturbance.

***B2: This study is innovative because it is the first study to dismantle mindfulness.*** There will be an 8-week intervention for each component/practice: 1) attention/focused awareness training (FA) and 2) acceptance/open monitoring training (OM), following Jacobson et al.'s classic dismantling paradigm (Jacobson et al., 1996). The study will investigate the effects of individual components/practices on clinical efficacy and mechanism of action in comparison to each other and the standard MBCT program, which includes both components.

***B3: This study is innovative because it is the first study to examine the practice-specific effects on the foundational PFC domain of wakefulness, on which both attention and emotion regulation depend.*** A number of studies have found that meditation is associated with improved PFC functioning, including attentional capabilities, emotion regulation and increased wakefulness (see above). To date, research has focused on attention and emotion regulation as the central mechanisms of meditation, with little regard for the related PFC domain of

wakefulness or sleep propensity. However, attention and emotion regulation are dependent on adequate wakefulness and compromised when wakefulness is low or sleep propensity is high (Banks & Dinges, 2007; Chuah et al., 2006; Couyoumdjian et al., 2009; Dinges et al., 1997; Drummond et al., 1999; Franzen et al., 2008; Goel et al., 2009; Harrison & Horne, 1998; Harrison et al., 2000; Ingre et al., 2006; Lim & Dinges, 2008; Lim et al., 2009; Nilsson et al., 2005; Thase et al., 1997; Van Dongen et al., 2003; Walker, 2009; West et al., 2009; Yoo, Gujar et al., 2007; Yoo, Hu et al., 2007; Zohar et al., 2005). Therefore knowledge of practice-specific effects on wakefulness will provide foundational information for understanding mechanisms of action. In order to provide the most comprehensive understanding of mechanism of action, this study will investigate all 3 domains of PFC functioning: Attention, emotion reactivity/regulation, and wakefulness.

***B4: If successful, this trial will provide:*** (a) The first, separate manualized treatment modules for the two core components of mindfulness with precise criteria for FA and OM meditation practices, (b) information about the clinical efficacy of each component/practice alone and in contrast to the standard combined treatment package and (c) information about the specific mechanisms of action for each component/practice. This information will identify *which* practices are most beneficial and *why* they are effective.

## 3.2 Potential Risks and Benefits

### 3.2.1 Potential Risks

- 1) Potential coercion. It is possible that patients may feel coerced into participating.
- 2) Confidentiality and loss of privacy. We will be collecting considerable information about the subject which may create some distress and could cause social and psychological risk if released inappropriately.
- 3) Discomfort during meditation: Meditation-based interventions may results in discomfort with attention to unpleasant thoughts, feelings or body sensations. Some individuals may experience an initial increase in undesirable feelings with increased attention to them.
- 4) Discomfort during assessments: Some participants may feel uncomfortable answering personal questions about their psychological health. The physiological recording electrodes may cause mild skin irritation. Some of the stimuli may be unpleasant or graphic.
- 5) Risk of adverse events during the study. It is possible that some patients will have an adverse event during the study, including failure to respond to treatment, worsening of depressive symptoms, suicidal ideation or behavior, or other adverse events.

### 3.2.2 Potential Benefits

A major goal of this study is to assess the differential impact of two commonly used forms of meditation practice. Thus, this project will provide much better information about active ingredients in a popular intervention. Furthermore, these studies may provide information to clinicians about how two common forms of meditation may work differently and may be better

suited for some patients than others. This will allow clinicians to administer the best treatment to respond to patients needs and promote wellbeing.

## **4. STUDY OBJECTIVES**

### **4.1 Primary Objective**

•**Aim 1:** Provide training in meditation-based clinical trials for affective disturbances, psychophysiology, biostatistics research methods, and ethical conduct in research.

•**Aim 2:** To create two separate treatment modules with specific criteria for the two core components and practices of attention training/focused awareness (FA) and open monitoring (OM)

•**Aim 3:** To establish the effect of FA and OM vs MBCT on depression and negative affect

|                            | Objective | Self-report |
|----------------------------|------------------|--------------------|
| Depression/negative affect | IDS interview    | DASS               |
| Positive affect/wellbeing  |                  | PANAS, WBS         |

### **4.2 Secondary Objectives**

•**Aim 4:** To assess and compare the effects of FA, OM and MBCT on subjective and objective measures of 3 domains of PFC functioning:

| PFC Domain               | Objective                  | Self-report |
|---------------------------------|-----------------------------------|--------------------|
| attention                       | SART                              | FFMQ, MAAS         |
| emotional reactivity/regulation | ERRT                              | DERS, SCO          |
| wakefulness                     | 5-9 HZ EEG power
sleep latency | KSS                |

•**Aim 5:** To determine which neurobehavioral processes (attention, emotion regulation, wakefulness) drive the clinical benefits of mindfulness training, independent of treatment allocation or practice type.

### **4.3 Exploratory Objectives**

To assess factors other than type of mental training that may impact outcome, including therapist-level (competence) and participant level factors (compliance).

## **5. STUDY DESIGN**

## 5.1 Flow Chart for study Design

[figure not shown]

## 5.2 Description of the Study Design

This dismantling study will be a 3-armed controlled trial that compares the effects of attention/FA, acceptance/OM and MBCT (combined FA-OM) on clinical efficacy and three domains of PFC functioning in 105 individuals with mild-severe depression and high negative affect. The design is based on Jacobson's classic 3 armed dismantling study (Jacobson et al., 1996) which compares single elements of a treatment package to the full, combined package.

**The number of study arms:** 3

**Name of Interventions:** Mindfulness-Based Cognitive Therapy; focuses awareness meditation; open-monitoring meditation

**Single or multi-center:** single

**Healthy or sick population:** Individuals with mild-severe affective disturbances will comprise the sample because they represent the most frequent users of meditation-based therapies, and because depression and anxiety represent some of the world's largest health burdens (183-185). This representative sample includes individuals who are both above and below the DSM-IV diagnostic threshold for major depressive disorder (MDD) and although not required, a past history of MDD and/or co-morbid anxiety symptoms are likely (37). Current psychiatric in-patients will not be eligible for the study.

**Description of study groups/arms including sample size**

The 90 anticipated completers will be nearly equally divided into each arm: FA, OM, and MBCT will each have approximately 30 participants. See [flow chart](#).

**Approximate time to complete study enrollment:** 36 months

**The expected duration of subject participation:** 20 weeks (including follow-up)

**A description of the sequence and duration of all trial periods, including follow-up (specify individual participants vs. entire trial)**

For individual participants:

After screening, and successful completion of baseline assessments, groups of participants will assigned to either the 1.) focused-awareness, b.) open-monitoring, or c.) traditional mindfulness-based cognitive therapy arm. Each treatment lasts for eight weeks, followed by a post-treatment assessment, and 3-month follow-up interview.

**Timeline overview of the entire award (years 1-5)**

Preparation for this study will start in year 1-2, including treatment module development/refinement, training in assessments and participant recruitment. The original grant timeline allocated a minimum of 3.5 years (42 months) and a maximum of 4 years (48 months) to complete the treatment and data collection portion of the K-award. If the first treatment begins in the spring of 2013, then data collection is scheduled to be complete in Aug 2016 (42 months) or Dec 2016 (48 months).

The total target recruitment is 105 enrolled/90 completers. The number of groups and number of participants per group will depend on recruitment rates, but is estimated to be 9-12 groups of 8-12 enrolled (7-10 completer) participants. Each “group” requires a four month block of time that contains pre and post assessments and 2 months of treatment.

Thus, the plan for the next 3 cycles would be to run one group in the spring 2013, one in the summer 2013 and one in the fall of 2013. The number of completers for the first (spring 2013) group will be known by June 1st 2013.

**Methods for collecting data for assessment of study objectives:**

Data collection methods include clinical interviews, laboratory-based assessments, and self-report questionnaires (see Procedures Manual for details)

**Primary and secondary outcomes to be measured during the trial**

The primary objective is to assess and compare the effects of three types of meditation practices (FA, OM, MBCT) on emotional disturbance and wellbeing.

Secondary objective are 1) to assess and compare the effects of FA, OM and MBCT on subjective and objective measures of 3 domains of PFC functioning: attention, emotional reactivity/regulation and wakefulness and 2) To determine which neurobehavioral processes (attention, emotion regulation, wakefulness) drive the clinical benefits of mindfulness training, independent of treatment allocation or practice type.

#### **Assessments:**

All assessments will be made on all study participants regardless of study arm

There are several type of assessments:

Screening (see [screening section](#) and procedures manual

Clinical Interviews (pre-treatment and 3 month follow-up)

Self-report questionnaires (pre-post and during treatment, and 3 month follow up) Laboratory

based assessment (pre-post treatment)

*See Procedures Manual for details*

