### **5.3 Study Endpoints**

#### **5.3.1 Primary clinical Endpoint**

**Depression, negative affect and wellbeing:**

|                            | Objective | Self-report |
|----------------------------|------------------|--------------------|
| Depression/negative affect | IDS interview    | DASS               |
| Positive affect/wellbeing  |                  | PANAS, WBS         |

Inventory of Depressive Symptomatology- Clinician Rated (IDS-C30) (Rush et al., 1986; Rush et al., 1996)

The Depression, Anxiety Stress Scale (DASS) (Brown et al., 1997; Crawford & Henry, 2003; Lovibond & Lovibond, 1995)

Positive and Negative Affect Schedule – Expanded Form (PANAS-X ) (Watson & Clark, 1994)

The Wellbeing Scale (WBS)(Ryff, 1989)

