### 9.7

### **Post Treatment Assessment**

After the 8th class, participants repeat the baseline assessment procedures (sleep diaries, z-machines, self-report questionnaires and laboratory assessments).

In addition to outcome questionnaires, participants will also complete questionnaire to their experience of the therapist and the treatment experience. See section on [Therapist Adherence](#)

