### 9.8

### **Assessment**

### **3 Month Follow-up**

Three months after the post-treatment assessment, the participants returns for an in-person clinical assessment interview (IDS, PANAS, DASS, WBS). The participant will also complete a

3rd set of self-report questionnaires. For details, see Table 2.1 Timeline and Summary of Assessments in the Procedures Manual.

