### 11.3.2 Primary Analyses:

**To asses and compare the effects of FA and OM modules on clinical efficacy vs standard MBCT** Multilevel Modeling (MLM) will be used to compare the trajectories of clinical improvements in affective states (IDS, DASS PANAS, WBS) for each treatment.

Level 1 variables will include depression, negative affect and wellbeing scores at multiple time points.

Level 2 variables will include treatment type, meditation practice amount and demographic variables (age, sex, education). A MLM approach (Bryk & Raudenbush, 1992) was chosen for analysis because it is well suited to repeated measures designs, yields more information than ANOVAs (i.e. allows for individual growth curves), has the ability to retain missing cases, and fits my training goals of advanced statistical analysis skills for treatment research.

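### The schedule gives the clinician-rated depression score (IDS) two occasions, too few for the individual growth curves of the primary analysis, and no section prespecifies adjustment for its baseline value

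*Protocol*

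**What the plan says.** **Schedule.** The list of assessments in protocol section 5.2 gives "Clinical Interviews (pre-treatment and 3 month follow-up" and, separately, "Self-report questionnaires (pre-post and during treatment, and 3 month follow up". Section 9.7 says that after the last class "participants repeat the baseline assessment procedures (sleep diaries, z-machines, self-report questionnaires and laboratory assessments"; no clinical interview is in that list. Section 9.8 says that three months later the "participants returns for an in-person clinical assessment interview (IDS, PANAS, DASS, WBS".

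**Status of the IDS.** Section 5.3.1 names the "Inventory of Depressive Symptomatology- Clinician Rated" scale among the primary measures. It is the only entry in the objective column; DASS, PANAS and WBS are self-reports.

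**Model.** Section 11.3.2 compares trajectories of all four scales by multilevel modelling. It states that "Level 1 variables will include depression, negative affect and wellbeing scores at multiple time points", and one reason for preferring the method to ANOVA is that it "i.e. allows for individual growth curves". Level 2 holds treatment, practice amount, age, sex and education. The baseline score is not on that list.

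**The concern.** The analysis section describes repeated scores from which individual curves can be drawn. The schedule supplies them for the three self-report scales but not for the IDS, which has a start and an end and nothing between.

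Two things follow. The feature that helped to justify the method is unavailable for the one clinician-rated primary scale. And once individual slopes are dropped, the result depends on how the baseline score enters the model, which section 11.3.2 does not say. The trial exists to estimate effect sizes for a larger trial (sections 11.1 and 11.4.1), so the precision of the IDS contrast matters directly.

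**Working it through.** **1. How many IDS occasions?**
- Section 5.2: interviews before treatment and at 3 months.
- Section 9.3 describes baseline as questionnaires and laboratory work; the IDS belongs to the screening interview (section 9.1.2). Repeating the baseline procedures under section 9.7 therefore adds no IDS.
- Section 9.8: IDS at 3 months.

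The scheduled count is two. The self-report scales have at least three.

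**2. The plan's own figure.** Section 11.4.4 gives N = 90 for 80% power: repeated-measures interaction, 3 groups, 2 measurements, alpha 0.05, d = 0.335. Take f = d/2 = 0.1675 and assume a correlation of 0.5 between measurements. The protocol states none; 0.5 reproduces its result.
- Noncentrality = f² × N × m / (1 − ρ) = 0.1675² × 90 × 2 / 0.5 = 10.10, on 2 and 87 degrees of freedom.
- Power is 0.805. The minimum N is 89, or 90 in equal arms.

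The stated figure reproduces, and it already rests on two measurements.

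**3. Can individual slopes be identified?** Let the intercept variance be a, the slope variance b, their covariance c and the residual variance s, with occasions at 0 and t.
- Var(first) = a + s
- Var(second) = a + 2tc + t²b + s
- Cov = a + tc

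That is three equations in four unknowns; the rank is 3 of 4, so the model is not identified. With three occasions, for example 0, 2 and 5 months, there are six moments and the rank is 4 of 4.

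**4. What can be fitted?** A random-intercept model with arm, time and arm-by-time can. One complete two-occasion dataset was simulated with 30 per arm and correlation 0.5. Standard errors of an arm contrast were:

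| Analysis | SE |
|---|---|
| Random intercept, baseline means free by arm | 0.227 |
| Change score | 0.227 |
| Mixed model, common baseline mean | 0.200 |
| 3-month score adjusted for baseline | 0.192 |

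The first two also gave the same estimates (−0.422 and −0.156).

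**5. Size.** Let r be the correlation between baseline and 3-month IDS, with equal variance (set to 1) at both occasions.
- Change score: 1 + 1 − 2r = 2(1 − r)
- Adjusted for baseline: 1 − r²
- Ratio: (1 − r)(1 + r) / [2(1 − r)] = (1 + r)/2

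| r (assumed) | Change | Adjusted | Ratio | Reduction | Adjusted N matching 90 |
|---|---|---|---|---|---|
| 0.3 | 1.40 | 0.91 | 0.65 | 35% | 58.5, so 59 |
| 0.5 | 1.00 | 0.75 | 0.75 | 25% | 67.5, so 68 |
| 0.7 | 0.60 | 0.51 | 0.85 | 15% | 76.5, so 77 |

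Class clustering is ignored throughout.

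**The case against.** **The two-occasion count may be incomplete.** Section 7.2 speaks of blinded assessors at 8 weeks as well as 3 months. Section 10.3.1 lists IDS interviews under scheduled safety collection, with change measured from the last assessment. Section 10.2.2.5 collects endpoint data at discontinuation. Details are deferred to the Procedures Manual, which is not part of the document reviewed. This stands as a reason to reconcile rather than assume. But none of these sections schedules a week-8 IDS, and sections 5.2 and 9.7 read against one. If one is taken, those two sections need correcting instead.

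**The protocol never writes a random slope for the IDS.** Growth curves appear as a general merit of the method, beside its ability to keep incomplete cases. A reader might infer that no multilevel model can be fitted to the IDS. That is not so: the random-intercept form fits, and only individual slopes are out of reach.

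**The inefficient form is not chosen.** A reader might also infer that the plan commits the IDS to a change-score analysis. Section 11.3.2 does not say how baseline enters, and change scores are named only for the secondary regression in section 11.3.3.2. The equivalence needs complete data and free baseline means. What remains is that nothing points the other way either: baseline score is absent from Level 2, and section 7.1.4.3 brings baseline differences into the analysis only if they are found.

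**Adjusting the 3-month score alone has a price.** It drops participants without that score, whereas section 11.6 keeps everyone allocated. This stands, and it shapes the fix.

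**Conclusion.** The point holds for the IDS, and in limited form. As scheduled, the IDS has two occasions; section 11.3.2 treats it as a trajectory with individual growth curves; individual slopes are not identified. No section prespecifies adjustment for baseline IDS, so the plan leaves open an analysis equivalent to a change score.

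Against that form, the error variance that could be saved is 15% to 35% for r from 0.7 down to 0.3. The range is assumed; it also takes equal variances at the two occasions and sets class clustering aside. It measures what a better specification gains, not a loss to which the plan is committed.

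A reader might infer that the trial is underpowered as a result. The documents do not support that: the sample size calculation uses two measurements and reproduces. The self-report primary scales, with three or more occasions, can support growth curves.

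**What to change.** 1. Reconcile sections 5.2, 7.2, 9.7, 9.8 and 11.3.2 on whether the IDS is taken at week 8, and state its occasions explicitly.
2. If it is not taken then, specify for the IDS a two-occasion mixed model that constrains baseline means to be equal across arms and includes the class effect. The constraint is reasonable because baseline precedes randomisation (section 7.2). The model stays within the planned method and keeps participants who lack a 3-month score. The alternative is the 3-month score with baseline IDS as covariate and the class effect, with missing scores handled so that all allocated participants remain.
3. Limit individual growth curves to DASS, PANAS and WBS.

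The cost is wording in the protocol and the analysis plan. No further interview, participant or data item is needed, since baseline IDS is already collected.
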